An overview of the data collection procedure is given in Fig. 2 and presented in full as follows:At the research visit, participants are placed in different rooms and individually answer the questionnaires REAGERA-S20 and REAGERA-N respectively. The next of kin are also asked to complete the following scales and questionnaires: the UCLA loneliness scale [24], the ZBI [20], the FAQ [35], the NPI-Q [9], the relationship reward questionnaire [46] and the CAMI [13, 34].Semi-structured interviews are then conducted with the person with dementia and their next of kin separately and simultaneously. The two researchers conducting the interviews are blinded to the answers given by the participants in the questionnaires. The interview starts with general background questions and moves on to questions about exposure to abuse. Initially, open-ended questions about negative experiences and difficulties in the relationship are asked. Thereafter, a more structured part of the interview is conducted in which specific questions about physical, psychological, sexual and financial abuse as well as neglect are asked. A digital interview guide is used, in which the researcher records the answers given by the participant to questions about different forms of abuse. If the participant reveals any kind of abusive experiences, an in-depth qualitative interview about the experiences is conducted at any time during the interview. Interviews are recorded and transcribed verbatim which allow for a later review of content as well as qualitative analyses. For the person with dementia, the questions in the Tilburg Frailty Indicator [18, 29] and relationship reward questionnaire [46] are also included in the interview.At the end of the individual interviews, the researchers check the answers given by the participant in REAGERA-S20 or REAGERA-N and compare them to the responses recorded in the digital interview guide during the interview. This allows for clarification of inconsistent responses and a preliminary classification of the person with dementia as abused or not abused based on the information provided in each individual interview.After the individual interviews have been completed, the two researchers compare the results from each interview. If needed, and with permission obtained individually from the participants, a joint concluding interview is conducted. This interview again allows for clarifying possible inconsistencies.After the interviews are completed, the two researchers together make a new classification of abuse status, considering information from both interviews. It is also noted if abuse earlier in life happened before the age of 18, between 18 and 60 or after the age of 60. In addition, the type of relationship with the perpetrator is noted. This information is collected to be able to understand false negatives, i.e. what types of abusive experiences are not captured by the REAGERA-S20 and REAGERA-N.One follow-up phone call is made after the interview to inquire about negative effects of participating in the study or if participation has given rise to any thoughts or questions. If there are indications of emotionally stressful or traumatic reactions of participating in the interview, relevant referrals to societal resources can be made at this stage.All interviews are recorded and transcribed verbatim. Thereafter, a review of the classification of participants as abused or not abused made during the interviews is conducted, using the transcript as a reference. The review is made by at least two researchers to make sure that similar classifications are made for all participants concerning kinds of experiences that constituting abuse. The final classification will be used as the gold standard against which the validity of the screening instruments is measured. If there is doubt whether an experience should be classified as abusive or not, discussions will be held within the research group and the Toronto Declaration [44] and the CDC definition and core elements of elder abuse [23] will additionally be used for the assessment. The following classification is used:For the person with dementiaReporting or not reporting abusive experiences during the past 12 months.Reporting or not reporting abusive experience earlier in life, i.e. more than 12 months ago.For the next of kinReporting or not reporting own exposure to abuse by the person with dementia during the past 12 months.Reporting or not reporting own perpetration of abuse towards the person with dementia during the past 12 months.Reporting or not reporting that the person with dementia has been exposed to abuse by another person during the past 12 months.Reporting or not reporting that the person with dementia has been exposed to abuse earlier in life, i.e. more than 12 months ago.

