### Statistical analysis plan

#### Aim 1: Testing the validity of REAGERA-S20 and REAGERA-N

Primary outcomes:Criterion validity will be assessed by calculating sensitivity, specificity, positive and negative likelihood ratio as well as positive and negative predictive value of each tool using the final classification made after interviewing both the person with dementia and the next of kin, i.e., the previously described step 7. Only participants for which data is available from both the person with dementia and next of kin will be included in the analyses. For REAGERA-S20, one or more positive answers in part two will be classified as reporting abusive experiences during the past 12 months. One or more positive answers in part three will be classified as abusive experiences earlier in life. For REAGERA-N, one or more positive answers to items concerning perpetration of abuse by next of kin in part two (no 1,3,6–8, 10) or any of the items in part three about witnessing abusive acts will be classified as abuse of the person with dementia during the past 12 months. Affirmative answers to items in part four will be classified as abusive experiences from earlier in life.Test the predictive value of the introductory screening questions in part one of each instrument to identify abusive experiences as identified in part two as well as the final classification of participants as abused or not abused. The introductory screening questions are answered on a three-point ordinal scale (“never,” “sometimes,” “often”). A sum score will be calculated for all items and the best threshold for discriminating between abused and not abused participants will be calculated using a Receiver Operating Curve (ROC) Analysis. We will also examine if one item or a combination of specific items are most likely to predict abusive experiences.

Secondary outcomes:

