Data collection is carried out on one occasion. This includes both answering the REAGERA-S20 or REAGERA-N, individual interviews and the joint interview. This choice was made to assure the safety of participants. If the questionnaires were sent home to be filled out beforehand, privacy of answers could not be assured. However, this procedure means that there is very little time between filling out the instruments and participating in the interview. It is therefore likely that participants recall their answers in the questionnaires when the interview is conducted. This may be considered as a limitation because responses in the questionnaire and in the interview are not completely independent. However, the aim of the interview is to reveal all experiences of abuse and, hence, it is rather considered a strength if some participants are prompted to remember and disclose experiences that may otherwise have not come up in the interviews.

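### Interviewers see the participant's REAGERA answers and re-query inconsistencies before they classify abuse, so the reference standard is informed by the test it is meant to judge

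*Protocol article*

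**What the plan says.** The sequence is set out in the Protocol article under Participants and procedure (Full scale test of instruments).

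- **Step 2.** "The two researchers conducting the interviews are blinded to the answers given by the participants in the questionnaires". Answers to the structured abuse questions are entered in a digital guide during the interview.
- **Step 3.** At the end of each individual interview "the researchers check the answers given by the participant in REAGERA-S20 or REAGERA-N and compare them to the responses recorded" in that guide. The stated use is: "This allows for clarification of inconsistent responses and a preliminary classification of the person with dementia as abused or not abused".
- **Step 4.** The two researchers compare their interviews and, if needed and permitted, hold a joint interview. "This interview again allows for clarifying possible inconsistencies".
- **Step 5.** The two researchers classify again, using both interviews.
- **Step 7.** At least two researchers review the classification "using the transcript as a reference". "The final classification will be used as the gold standard against which the validity of the screening instruments is measured".

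Under Aim 1 of the Statistical analysis plan section, the primary accuracy measures are calculated "using the final classification made after interviewing both the person with dementia and the next of kin". The secondary analyses use a single individual interview as reference. A next of kin included alone goes through steps 1–3 and 6–7, so the step 3 check applies there too.

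The Discussion accepts that questionnaire and interview are not fully independent, because participants may recall their answers, and adds that "it is rather considered a strength if some participants are prompted to remember and disclose experiences". It does not mention the researchers' own look at the questionnaire.

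**The concern.** An accuracy study needs a reference that is established without knowledge of the index test. Here the blinding ends before the first classification, and the questionnaire decides which interview answers are queried again. If a positive questionnaire leads to a disclosure that the blinded interview had not produced, the questionnaire is credited with detecting a case that it helped to put into the reference. If a negative questionnaire leads to an interview answer being toned down, a miss disappears.

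Criterion validity is the primary outcome for both new instruments. Part of the reported sensitivity and specificity could therefore reflect agreement after reconciliation. The article describes no classification fixed before the check, so its readers could not tell how large that part is.

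**Working it through.** **Order of events.** Blinded interview, questionnaire opened, inconsistencies clarified, preliminary classification, joint interview if needed, joint classification, transcript review. Nothing that serves as a reference precedes the opening of the questionnaire. The step 7 review does not undo this if the transcript includes the clarification.

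**Inputs from the article.** 80 pairs. Pilot prevalence 10/24 = 41.7%, which agrees with the stated 42%. Planning prevalence 40%, hence 0.40 × 80 = 32 abused and 48 not abused. Planning sensitivity 80%. The article gives no figure for how often the check changes a classification, so every share below is an assumption, as are the starting specificities and the 70% sensitivity.

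**Method.** Let TP, FN, TN and FP be the counts against the blinded interview. Let u be the share of questionnaire-positive, interview-negative cases reclassified as abused, and v the share of questionnaire-negative, interview-positive cases reclassified as not abused. Then

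- sensitivity = (TP + u·FP) / (TP + u·FP + (1 − v)·FN)
- specificity = (TN + v·FN) / (TN + v·FN + (1 − u)·FP)

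For one instrument against its own blinded interview, both expressions increase in u and in v.

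**Start at 70%/85%.** TP 22.4, FN 9.6, TN 40.8, FP 7.2. With u = 50% and v = 0, 3.6 cases move: sensitivity 26.0/35.6 = 73.0%, specificity 40.8/44.4 = 91.9%.

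**Start at 80%/80%.** TP 25.6, FN 6.4, TN 38.4, FP 9.6.

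| u | v | Sensitivity | Specificity |
|---|---|---|---|
| 0 | 0 | 80.0% | 80.0% |
| 10% | 10% | 26.56/32.32 = 82.2% | 39.04/47.68 = 81.9% |
| 25% | 25% | 28.0/32.8 = 85.4% | 40.0/47.2 = 84.7% |
| 50% | 50% | 30.4/33.6 = 90.5% | 41.6/46.4 = 89.7% |
| 10% | 0 | 26.56/32.96 = 80.6% | 38.4/47.04 = 81.6% |
| 25% | 0 | 28.0/34.4 = 81.4% | 38.4/45.6 = 84.2% |
| 50% | 0 | 30.4/36.8 = 82.6% | 38.4/43.2 = 88.9% |

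**Two informants.** The primary reference combines both interviews. Take REAGERA-S20 at 70%/85% with half of its false positives reclassified, and suppose that two S20-negative pairs enter as abused through the REAGERA-N check. Sensitivity becomes 26.0/(35.6 + 2) = 26.0/37.6 = 69.1%, below the starting 70%. Specificity becomes 38.8/(38.8 + 3.6) = 91.5%.

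**Against true abuse.** Assume a true accuracy of 70%/85%, 40% prevalence, and questionnaire and interview errors independent given true status.

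- Interview with sensitivity 90% and specificity 100%, all truly abused questionnaire-positive cases recovered by the re-query: 72.2%/85.3%, slightly above truth.
- Interview with sensitivity 80% and specificity 95%, half of such cases recovered: 67.9%/81.8%. This is above the 65.3%/78.2% that the blinded interview would give, but still below truth.

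**The case against.** The article has a reasonable defence. No objective standard for abuse exists, the interview aims to bring out every experience, and a re-query may reveal real cases that a single blinded pass would miss. The classification rests on what is said in the interview, at least two researchers review it against the transcript, and doubtful cases go to published definitions.

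This defence rules out three stronger readings that a reader might infer:

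- *The questionnaire is part of the gold standard.* It is not. No questionnaire score enters the classification rule. The reference is informed by the index test and does not contain it.
- *Only disagreements are re-examined, so abuse missed by both is never found.* The text does not support this. Such abuse can enter through the other informant, the joint interview or the step 7 review, which covers all participants.
- *Reported sensitivity and specificity are biased upward.* This is certain only for one instrument against its own blinded interview. It is not established against true abuse or for the combined reference.

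The size is also open. The larger sensitivity gains need interview-disclosed abuse to be relabelled as no abuse, which the article nowhere describes; step 5 expects false negatives to remain and collects data to explain them. With additions only, the shift in sensitivity in these examples (at most about 3 points) is small beside a 95% half-width of about 14 to 16 points with 32 cases. Specificity can move more, by 7 to 9 points at the assumed 50% share. Whether the step 7 reviewers are masked is not stated and may be settled in the full protocol.

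What stands is that the unblinding before classification is a stated procedure, and that the Discussion's concession covers participants' recall only. Finding more real cases is a good aim, but it does not make the reference independent of the questionnaire.

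**Conclusion.** The point holds in this form: the step 7 gold standard and the single-interview references are formed after the interviewers have seen the questionnaire and acted on it. For each instrument, resolving its own discordances towards the questionnaire raises both accuracy measures relative to a blinded interview. The illustrative size is 70%/85% to 73%/92% with half of the false positives reclassified, or about 2 to 10 points on both measures from 80%/80% with 10% to 50% of discordances reclassified. These shares are assumptions, not estimates. For the two-informant primary reference, and against true abuse, neither the direction nor the size of the net effect can be determined from the article. Because the primary outcome is affected and the effect cannot be bounded, a result against a blinded reference is needed.

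**What to change.** 1. For each participant, derive a pre-check classification from the digital guide responses recorded before the questionnaire was opened. If those entries were overwritten, use the transcript up to the check. The reviewers should be masked to the questionnaire answers.
2. For any remaining visits, lock this entry before the questionnaire is opened. Recruitment was planned to finish at the end of 2024, so this may apply to few or none.
3. Combine the pre-check classification over both informants and compute the sensitivity and specificity of REAGERA-S20 and REAGERA-N against it.
4. Report these next to the results for the post-check classification, which can stay as it is, joint interview included. Rest accuracy claims on the blinded reference, or qualify them explicitly where the two differ.
5. Do the same for the single-interview secondary analyses, including next of kin who take part alone.

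The cost is a masked re-review of up to 80 pairs, plus any next of kin included alone, and one extra table. Accuracy may look less favourable, and some real cases disclosed only on re-query will be left out of the blinded reference, which is why both sets of results should be shown. The retrospective route depends on the guide entries being unaltered or on the check being identifiable in the transcript; the article confirms neither.

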
**Fig. 2 Fig2:**
[figure not shown]
Overview of the data collection procedure

When a next of kin is included alone, steps 1–3 and 6–7 are conducted.

The need for societal support for both the person with dementia and the next of kin will be evaluated at the end of each individual interview as well as at the joint interview and follow up call. This gives repeated opportunities to provide relevant referrals if needed, both in relation to potential AOP and in relation to potential stressful or traumatic reactions in relation to participating in the study.

After the interviews have been completed, the REAMI is sent electronically to a health or social care provider who has knowledge about the person with dementia, and they are asked to fill it out.

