**Method:**

People with mild to moderate dementia (*n* = 80) and their next of kin (*n* = 80) are recruited at health and social care facilities providing care to people with dementia. In cases of severe dementia, only next of kin is included. At the time of data collection, participants fill out the instruments and are thereafter interviewed, first separately and then jointly by researchers about their abusive experiences. The interviews are used as a gold standard for calculating the properties of the instruments, e.g., sensitivity and specificity, but will also be used for qualitative analysis concerning the experiences of abuse. Health and social care professionals that are well acquainted with the participants fill out the REAMI and results will be validated using the results of the interviews as the gold standard.

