### Full scale test of instruments

#### Participants and procedure

Participant recruitment started in spring 2023 and is planned to continue until the end of 2024. Participants are recruited from three outpatient memory clinics in Sweden, from primary healthcare centres and municipalities caring for people with dementia.

Inclusion criteria for people with dementia are a dementia diagnosis and having a cognitive decline assessed as GDS 4 or 5. Inclusion criteria for next of kin is being next of kin to a person diagnosed with dementia, with the degree of cognitive decline assessed as GDS 4–7. Exclusion criteria for both people with dementia and next of kin are severe psychiatric disorder, not being able to answer the questionnaires or participate in an interview, e.g. due to insufficient proficiency in Swedish, aphasia, hearing loss or similar. In addition, people with dementia experiencing symptoms that may be exacerbated by study participation or make results less reliable (e.g. paranoia) are excluded.

Inclusion and exclusion criteria are assessed by professionals working at each centre recruiting participants and, when needed, in conjunction with a member of the research team. Written information about the study as well as about available societal support for victims of AOP is handed out in conjunction with contact with a care provider at the clinic or municipality. A researcher thereafter contacts potential participants and if needed gives additional information about the study. Subsequently, a time of interview is arranged for those agreeing to participate. Interviews are mainly conducted at the healthcare facilities where participants are recruited but if needed home visits can also be provided. A prerequisite for a house call is that interviews can be carried out in two separate rooms.

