Next of kin may be included alone but people with dementia are only included together with their next of kin to assure that someone is there after data collection and, if needed, can assist in seeking help. This decision was made to assure safety for participants but may result in a selection bias. It is likely that older people suffering with severe forms of violence from a next of kin may choose not to participate. However, previous research [8] as well as the results of our pilot study suggest that next of kin are willing to disclose perpetrating acts of abuse. Also, in addition to providing a more comprehensive picture of potential abuse by the next of kin, interviewing both the person with dementia and the next of kin may facilitate disclosing other forms of abuse, e.g. by health or social care staff.

People with dementia and their next of kin are first interviewed separately and then together. To further assure safety and confidentiality for participants, the individual interviews are concluded with a discussion about what parts of the interviews may be shared in the following joint interviews. An assessment of the need to refer participants to relevant societal support organisations is also made together with participants at the end of both the individual and joint interviews. Participants are also telephoned within a few weeks of the data collection and asked about negative reactions to participating in the study. This provides a second opportunity to make relevant referrals for those reporting experiences of abuse or reporting stressful reactions to participating in the interview. Follow-up phone calls were also made in the pilot study and no severe negative reactions to participating in the study was reported. As an additional safety measure, information about societal support available in relation to AOP is handed out together with the information about the study. This assures that all participants as well as those choosing not to participate has information on where to turn for help if needed.

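### The REAMI is completed only after the interviews that supply its gold standard, with no stated blinding of the rater to what was disclosed, so its accuracy estimates are open to an avoidable bias.

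*Protocol article*

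**What the plan says.** The sequence is set out in the protocol article under Participants and procedure (full scale test). Both members of a pair complete their questionnaires, are interviewed separately, and may then be interviewed together. The text after Fig. 2 continues: "After the interviews have been completed, the REAMI is sent electronically to a health or social care provider". The abstract describes the raters: "Health and social care professionals that are well acquainted with the participants fill out the REAMI".

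The same section says that the need for support "will be evaluated at the end of each individual interview as well as at the joint interview and follow up call", and adds: "This gives repeated opportunities to provide relevant referrals if needed, both in relation to potential AOP". The Discussion gives the destination of referrals: "An assessment of the need to refer participants to relevant societal support organisations is also made together with participants". It also dates the last of these occasions: "Participants are also telephoned within a few weeks of the data collection". On location: "Interviews are mainly conducted at the healthcare facilities where participants are recruited".

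Under Aim 2 of the statistical analysis plan section, the REAMI is judged against the final abused/not abused classification. A ROC analysis picks the threshold, and the accuracy measures are then calculated at that threshold. The 24 pilot pairs are added to this analysis. The final classification (step 7) is a review of transcripts by at least two researchers.

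**The concern.** The REAMI is meant to capture what a professional can judge from ordinary acquaintance with the person. In this design the rating is made after the reference information has been elicited. A provider who hears of a disclosure from the family, or through support set in motion at the visit, may rate the person differently as a result. The section on the REAMI says its items cover signals of abuse as well as risk factors, scored by degree of agreement, so such knowledge could plausibly move the score.

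This is index-test review bias. Validating the Swedish REAMI is one of the three specific aims, and both the threshold and the accuracy figures come from these ratings. In routine use no research interview would precede the form, so accuracy that benefited from one would not carry over. The Discussion does take up non-independence, but only between the self-completed questionnaires and the interview. Its reasons (privacy of answers given at home, and the value of prompting recall in the interview) do not apply to a form sent electronically to a professional.

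**Working it through.** The plan states no figure on this point, so there is none to reproduce. The check is one of order, followed by an illustration.

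**Order of events**

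| Event | Position relative to REAMI dispatch |
|---|---|
| Individual interviews and any joint interview | Before (stated) |
| Support assessment at those interviews, referral possible | Before (follows from the above) |
| Follow-up call (step 6), a further referral occasion | Not stated |
| Final classification from transcripts (step 7) | Not stated |

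**Blinding.** Interviewers are blinded to the REAGERA answers. Nothing is stated about the REAMI rater and interview findings, or about the step 7 reviewers and the REAMI. The REAMI is not listed as an input to step 7.

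**How many participants this concerns**
- Pilot prevalence (Sample size section): 10/24 = 41.7%, matching the stated 42%.
- Pairs in the REAMI analysis: 80 + 24 = 104.
- Expected abused at pilot prevalence: 104 × 10/24 = 43.3, about 43.

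The article does not say when the REAMI was completed in the pilot, so it is unknown whether the 24 pilot pairs are affected.

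**Illustration for sensitivity (assumed inputs).** Let s be the true sensitivity and f the share of would-be false negatives that become positive because the rater learned of the disclosure. Then

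apparent sensitivity = s + f(1 − s).

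| True s | f = 0 | f = 10% | f = 20% | f = 30% |
|---|---|---|---|---|
| 0.50 | 0.50 | 0.55 | 0.60 | 0.65 |
| 0.60 | 0.60 | 0.64 | 0.68 | 0.72 |
| 0.70 | 0.70 | 0.73 | 0.76 | 0.79 |
| 0.80 | 0.80 | 0.82 | 0.84 | 0.86 |

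At s = 0.60, about 43.3 × 0.40 = 17.3 abused participants would be missed. Converting 10–30% of them means 1.7 to 5.2 people, so a handful of informed raters would be enough to move the estimate by 4 to 12 percentage points.

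**Specificity.** If contact with the rater also follows distress in non-abused pairs, and a share g of true negatives is pushed above the threshold, apparent specificity = true specificity × (1 − g), which is lower. The document gives no value for g.

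**The case against.** The strongest reply is that no passage shows information reaching the rater. Referrals are described as going to societal support organisations, not to the REAMI provider. The joint interview needs each participant's permission, and each individual interview ends by agreeing what may be shared even within the pair. Holding interviews at the care facility does not mean that staff learn their content. Raters are chosen because they know the person, so abuse they knew of beforehand is legitimate input. All of this stands, and it makes the leakage a possibility and not a finding of fact.

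The objection to the arithmetic also stands. Both s and f are assumed, f = 0 is compatible with the text, and the formula supposes that f counts only raters who actually cross the threshold. The REAMI is a 22-item total score, so learning of abuse need not change the risk category. Nor is the direction certain: support can also be triggered by stressful reactions to taking part, which can occur where there was no abuse.

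Two stronger readings are tempting and should not be adopted. A reader might infer that the REAMI comes after every referral. The follow-up call is a later referral occasion, and its order relative to the REAMI is not given. A reader might also infer that the REAMI is completed before the gold standard is final, perhaps because transcription takes time. The text gives no such order, and an unfinished classification could not explain how a rater came to know it. It would only raise the separate question of whether the step 7 reviewers see the REAMI.

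The objection does not remove the stated sequence. Blinding detail may be held in a fuller protocol, but dispatch after the interviews is a choice that this article makes, without giving a reason for it.

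**Conclusion.** The point holds in limited form. The index test is completed after the interviews that form its reference standard, and after the support assessments made at the visit, by a care professional for whom no blinding to the disclosures is stated. That creates a route for bias in the REAMI's accuracy. Higher sensitivity and AUC are the most plausible result; lower specificity is possible too, so the net effect on the chosen threshold is not established.

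The size cannot be derived from the document. The 60–72% range rests wholly on an assumed true sensitivity of 60% and an assumed 0–30% conversion of misses, and its lower end means no bias at all. The document does not support saying that REAMI accuracy is inflated. It supports saying that the design leaves this open when a simple change of order would close the route.

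**What to change.** **Pairs not yet interviewed.** Once consent is given, send the REAMI before the interviews start, and ask the rater to answer from prior knowledge of the person. The form is already electronic, so the cost is small: consent must be in place before dispatch, and some forms will be collected for pairs who then do not attend.

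**Pairs already completed.** Recruitment was planned to run to the end of 2024 and the article appeared in August 2025, so this may be most or all of them. Use the electronic completion time, and any available record of study-triggered contact with the rater, for a sensitivity analysis reported beside the main result. The article does not say that such a contact record is kept. Excluding flagged pairs would also selectively remove abused participants, so this analysis cannot replace the main one. State the rater's possible awareness as a limitation.

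**Final classification.** Make the step 7 classification without access to the REAMI score, and say so. This costs nothing beyond withholding the score until the classification is locked.

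**Referrals.** Leave the referral procedure unchanged.
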